## Abstract

**Introduction:**

Heart failure with preserved ejection fraction (HFpEF) is characterised by severe exercise intolerance, particularly in those living with obesity. Low-energy meal-replacement plans (MRPs) have shown significant weight loss and potential cardiac remodelling benefits. This pragmatic randomised trial aims to evaluate the efficacy of MRP-directed weight loss on exercise intolerance, symptoms, quality of life and cardiovascular remodelling in a multiethnic cohort with obesity and HFpEF.

**Methods and analysis:**

Prospective multicentre, open-label, blinded endpoint randomised controlled trial comparing low-energy MRP with guideline-driven care plus health coaching. Participants (n=110, age ≥18 years) with HFpEF and clinical stability for at least 3 months will be randomised to receive either MRP (810 kcal/day) or guideline-driven care for 12 weeks. Randomisation is stratified by sex, ethnicity, and baseline Sodium Glucose Cotransporter-2 inhibitor (SGLT2-i) use, using the electronic database RedCap with allocation concealment. Key exclusion criteria include severe valvular, lung or renal disease, infiltrative cardiomyopathies, symptomatic biliary disease or history of an eating disorder. Participants will undergo glycometabolic profiling, echocardiography, MRI for cardiovascular structure and function, body composition analysis (including visceral and subcutaneous adiposity quantification), Kansas City Cardiomyopathy Questionnaire (KCCQ) and Six-Minute Walk Test (6MWT), at baseline and 12 weeks. An optional 24-week assessment will include non-contrast CMR, 6MWT, KCCQ score. Optional substudies include a qualitative study assessing participants’ experiences and barriers to adopting MRP, and skeletal muscle imaging and cardiac energetics using 31Phosphorus MR spectroscopy.

**Statistical analysis:**

Complete case analysis will be conducted with adjustment for baseline randomisation factors including sex, ethnicity and baseline SGLT2-i use. The primary outcome is the change in distance walked during the 6MWT. The primary imaging endpoint is the change in left atrial volume indexed to height on cardiac MRI. Key secondary endpoints include symptoms and quality of life measured by the KCCQ score.

**Ethics and dissemination:**

The Health Research Authority Ethics Committee (REC reference 22/EM/0215) has approved the study. The findings of this study will be published in peer-reviewed journals.

**Trial registration number:**

NCT05887271.

STRENGTHS AND LIMITATIONS OF THIS STUDYThis is a pragmatic, randomised controlled trial exploring the efficacy of a low-energy meal-replacement plan (MRP) on exercise intolerance.Primary endpoint is distance covered in a Six-Minute Walk Test, chosen in collaboration with people living with heart failure with preserved ejection fraction (HFpEF), given it is most reflective of exercise intolerance which is the key daily limiting factor of HFpEF.Addition of comprehensive imaging (echocardiography, skeletal muscle and cardiac MRI) will allow the assessment of potential mechanisms of benefit.The nested qualitative study will allow for exploration of the participants’ barriers and facilitators to long-term adoption of MRP and the implementation of lifestyle changes.Limitations include the relatively small sample size, aiming for proof of efficacy and the small number of centres may limit the generalisability of the findings to the wider HFpEF population living with obesity.

## Background

 Heart failure with preserved ejection fraction (HFpEF) is increasingly prevalent and associated with high symptom burden and significant functional impairment.^1 2^ Over 80% of patients with HFpEF are either overweight or obese^3^ and emerging evidence suggests that excess body fat plays a direct role in the development and progression of HFpEF.^4^,^6^ Excess visceral adiposity promotes inflammation, hypertension, insulin resistance and dyslipidaemia resulting in increased risk of cardiovascular (CV) events. It is also associated with adverse cardiac remodelling,^7 8^ reductions in myocardial perfusion reserve (MPR)^9^ and myocardial energetics,^10^ all of which are implicated in the pathogenesis of HFpEF. Furthermore, obesity predisposes to skeletal muscle dysfunction, sarcopenia and frailty which exacerbate exercise intolerance, the key symptom of HFpEF.^11^,^17^ In recognition of the pathophysiological importance that comorbidities play in the genesis of HFpEF, the recent heart failure guidelines advocate the treatment of obesity and other systemic diseases as key therapeutic targets in HFpEF.^18^

Recent evidence from the semaglutide in obesity-related HFpEF (STEP-HFpEF)^19^ and semaglutide in obesity and type 2 diabetes mellitus-related HFpEF (STEP-HFpEF DM)^20^ trials highlights weight loss as a promising therapeutic target for improving exercise tolerance and reducing symptoms in heart failure patients. The STEP-HFpEF trial demonstrated that weekly 2.4 mg semaglutide injections resulted in 10.6% greater weight loss and a 20.3 m improvement in the Six-Minute Walk Test (6MWT) (95% CI 8.6 to 32.1; p<0.001) compared with placebo.^19^ Quality of life significantly improved, with a mean KCCQ score change of 7.8 points (95% CI 4.8 to 10.9; p<0.001).^19^ Similar benefits were observed in the STEP-HFpEF DM trial,^20^ where semaglutide led to larger reductions in heart failure symptoms (mean KCCQ score difference of 7.3 points, 95% CI 4.1 to 10.4; p<0.001), a 14.3 m improvement in the 6MWT (95% CI 3.7 to 24.9; p=0.008) and greater weight loss (difference of −6.4 percentage points; 95% CI −7.6 to −5.2; p<0.001) at 1 year compared with placebo.^20^

Substantial weight loss comparable to pharmacotherapy can be achieved through lifestyle interventions. In the largest lifestyle study to date, a 2×2 factorial randomised controlled trial of 100 HFpEF patients with obesity was randomised into the diet (400 kcal/day deficit), exercise (1-hour thrice-weekly supervised exercise session), or a combination of both for 20 weeks.^21^ The small average weight loss of 7 kg in the dietary intervention was associated with a 7-point improvement in the KCCQ score (95% CI (2.6 to 12.3), p=0.004), small but significant rise in peak VO_2_ by 1.3 (0.8, 1.8) mL/kg body mass/min and a 26 m increase in 6MWT distance (difference (95% CI) 25.9 (11.9 to 40.2) m, p<0.001). Additionally, a non-significant numerical decrease in left ventricular (LV) mass and LV relative wall thickness and a trend in improvement in diastolic function was shown by echocardiography.^21^

Although evidence from randomised controlled trials indicates that weight loss improves exercise tolerance and reduces symptoms in obesity-related HFpEF, existing trials primarily involved Caucasian and male participants (50% females in STEP programme), limiting their generalisability. This is particularly relevant as non-white ethnicities and females are at risk of higher symptom burden from HFpEF, hospitalisations and adverse outcomes.^22^,^24^ Semaglutide, while effective, has side effects (between 13% and 18% of users experienced adverse events)^19 20^ and may not be suitable for all patients or desirable by those with polypharmacy or needle aversion. The dietary intervention in Kitzman *et al*’s study produced modest weight loss but was impractical, requiring individually prepared meals and the trial was conducted in an inpatient setting.^21^ Furthermore, the trials used basic CV phenotyping,^19^,^21^ leaving the effects on key HFpEF indices, such as left atrial and ventricular remodelling, aortic distensibility, MRP and cardiac fibrosis, unknown. In particular, changes in left atrial volume indexed (LAVi) have been shown to be of prognostic significance in HFpEF.^25^ Thus, there remain uncertainties relating to the mechanisms of benefit of weight loss on CV outcomes and the need for further study on the direct impact on CV remodelling. The impact on frailty, sarcopenia or body composition changes, and how those related to cardiac remodelling or exercise tolerance also remains unclear.

### Aims

The aim of this study is to assess the efficacy of an meal-replacement plan (MRP) in improving exercise intolerance, symptoms, quality of life, CV remodelling and skeletal myopathy in patients living with HFpEF and obesity.

The nested qualitative substudy aims to enhance our understanding of the attitudes and barriers to the adoption of MRP (see online supplemental appendix 3 for the interview topic guide) The musculoskeletal substudy will elicit the effects of weight loss on sarcopenia, muscle strength, composition and changes in skeletal muscle energetics in response to weight loss. At selected sites, the optional 31-Phosphorus cardiac MR spectroscopy (31P-MRS) to assess changes in skeletal muscle and myocardial energetics in response to weight loss.

The optional 24-week visit aims to provide data on delayed cardiac remodelling, and remote follow-up at 12 months will provide outcome data related to mortality and hospitalisations.

## Methods and analysis

### Trial design

The Mult-Ethnic, multi-centre raNdomised contolled trial of a low energy Diet for impriving functional status in heart failure with Preserved ejection fraction (AMEND-preserved) is an open-label, multicentre, randomised controlled trial conducted at secondary care hospitals in the UK in Leicester, Manchester, Leeds and Oxford. The trial is registered on ClinicalTrials.gov NCT05887271 with approval from the national research ethics service (22/EM/0215).

Potential participants will be identified from heart failure clinics, hospital wards, diagnostic departments, health records and waiting lists as detailed in figure 1. To enhance study accessibility and include under-represented groups, recruitment will extend to community settings such as faith centres and community groups, aiming to achieve a balanced ethnic mix. We collaborate with the Leicester Centre for Ethnic Health Research for guidance on broadening participation. Our recruitment strategies will be constantly monitored to ensure a wide representation of ethnicities and genders. All participants meeting the eligibility criteria (summarised in box 1) will be invited to participate in the study.

Box 1Eligibility criteria for inclusion in the AMEND Preserved trialInclusion criteriaEstablished clinical diagnosis of heart failure with preserved ejection fraction (HFpEF) (left ventricular ejection fraction >45%) made by a cardiologist or a primary care physician with heart failure expertise, or a heart failure specialist nurse.Clinically stable for ≥3 months (no admissions to hospital).Obesity (body mass index ≥30 kg/m^2^ if white European or ≥27 kg/m^2^ if Asian, Middle Eastern or black ethnicity).Age ≥18 years old.Exclusion criteriaInability to walk/undertake Six-Minute Walk Test.Inability to follow a low-energy meal replacement plan.HFpEF due to infiltrative cardiomyopathy (cardiac amyloidosis or sarcoidosis), genetic hypertrophic cardiomyopathy, restrictive cardiomyopathy/pericardial disease or congenital heart disease.Known heritable, idiopathic or drug-induced pulmonary arterial hypertension.Severe chronic obstructive pulmonary disease (forced expiratory volume in 1 s<1.0 L).Severe primary valvular heart disease.Anaemia (haemoglobin<100 g/L).Severe renal disease (estimated glomerular filtration rate <30 mL/min/1.73 m^2^).Unintended weight loss >5 kg in preceding 3 months.Symptomatic gallstone disease including biliary colic or recent cholecystitis (<3 months).Active substance abuse (drugs or alcohol).History of bariatric surgery in the last 3 years.Active illness likely to cause change in weight.Women who are pregnant or are considering pregnancy.People currently participating in another clinical research trial that is likely to affect diet or weight change.History of a severe mental illness including an eating disorder.Individuals with a diagnosis of type 1 diabetes mellitus.

**Figure 1 F1:**
[figure not shown]
Summary of trial flow. Participants in the Multi-Ethnic, multi-centre raNdomised, controlled trial of a low-energy Diet for improving functional status in Heart failure with Preserved ejection fraction (AMEND Preserved) trial will be recruited from secondary care and randomised 1:1 into meal replacement plan (MRP) or standard care (control) for a duration of 12 weeks. Primary outcome (Six-Minute Walk Test, 6MWT) will be collected at baseline and 12 weeks. Participants will be invited to participate in the optional qualitative interview and sarcopenia substudies, as well as offering an optional visit at week 24 to assess for delayed cardiac remodelling. Health outcomes will be collected remotely at 12 months. HFpEF, heart failure with preserved ejection fraction. CMR: cardiac magnetic resonance imaging, ECG: electrocardiogram

### Study visits

The study will comprise two main assessment visits, at baseline and 12 weeks, with an optional third visit at week 24. An outline of study visits and measures taken during each visit is shown in table 1. Participants will have the option to split the baseline and 12-week visits into two visits in close succession if undergoing the assessments in 1 day is too onerous. Participants will be offered reimbursement for travel. Lunch will be provided during each assessment visit.

**Table 1 T1:** Overview of assessments during study visits

	Baseline visit	Week 12 visit	Week 24 visit (optional)
Visit window		±3 days	±2 weeks
Eligibility assessment	✓		
Consent	✓		
Medical history and examination	✓		
Medication review and adjustment	✓	✓	
Demographics and height measurement	✓		
Body weight recording	✓	✓	✓
Blood pressure and heart rate	✓	✓	✓
Blood sampling	✓	✓	
ECG	✓	✓	
Echocardiography	✓	✓	
CMR	✓	✓	✓
Accelerometery	✓	✓	
Health coaching (in both arms at baseline then control arm only)	✓	✓	
6MWT	✓	✓	✓
Handgrip strength	✓	✓	
Questionnaires	✓	✓	✓

6MWTSix-Minute Walk Test

### Baseline visit

Following eligibility confirmation by the study clinician and after obtaining written informed consent (an example consent form is provided in online supplemental appendix), all participants will undergo a clinical review and medication adjustment with the study clinician(s) in line with current clinical guidance for HFpEF.^26^,^28^ All participants will proceed to have a comprehensive multiparametric phenotyping (assessments outlined below). All participant data will be anonymised and stored in a secure electronic database.

### 12-week data collection visit

At 12-week visit, baseline assessments as described below will be repeated alongside a comprehensive health review. Medications paused at the trial’s onset will be reassessed and resumed if necessary. Primary outcome will be collected on this visit; however, participants will be invited to take part in the optional substudies and additional visit at 24 weeks as detailed below.

Clinical records will be followed up and reviewed at 12 months for clinical outcomes.

### Data collection and management

The study team will input all data, with accuracy verified by the principal investigators (PIs). Data quality control will involve identifying missing data, outliers and discrepancies through systematic queries. Each participant will receive a unique study ID on enrolment. Anonymised participant data will be securely uploaded and managed using the Research Electronic Data Capture (REDCap) platform.

### Assessments at baseline and week 12 visits

The following assessments will be conducted in a single or split visit depending on the participant’s preference. The participants will attend after an overnight fast and a light meal will be provided postvenepuncture.

#### Anthropometric variables

Body weight and height will be measured to the nearest 0.1 kg and 1 cm, respectively. Brachial blood pressure (BP) will be obtained from the participant’s dominant arm in a seated position and an average of the last two measurements will be recorded. Ethnicity, smoking status and weekly alcohol intake, medical and medication history will be obtained by self-report and from clinical records where applicable.

#### Biochemical variables

Fasting blood sample will be taken for biochemical profile for diabetes screening/glycaemic control in those with known type 2 diabetes (T2D) (fasting glucose and glycated haemoglobin (HbA1c), respectively), liver and kidney function, lipid profile (including total cholesterol, high-density lipoprotein (HDL), non-HDL cholesterol and triglyceride content), assessment of blood markers of inflammation (C reactive protein, CRP) and measures of cardiac stress (high sensitivity-troponin and N terminal brain-natriuretic peptide levels, NT-proBNP). Additional plasma and serum will be stored for future metabolomic, proteomic and genomics analyses subject to additional funding.

#### Questionnaires

The KCCQ^29^ will be used to assess disease-specific quality of life. All participants in the study will also undergo simple assessment of frailty and sarcopenia including the Edmonton Frail Scale (EFS) questionnaire, which provides an objective measure of frailty and the impact on physical, cognitive, social and general health domains.^30^ The ‘Strength, Assistance with walking, Rise from a chair, Climb stairs and Falls’ (SARC-F) questionnaire assesses strength, mobility and falls risk.^31^

#### Skeletal muscle assessment and strength testing

Participants’ quadriceps muscle volume will be quantified through MRI, complemented by handgrip strength testing via a dynamometer, with participants seated, elbow resting at a 90° angle, performing maximal effort squeezes.^32^ All three readings will be recorded but the highest is taken as a key measure. These baseline assessments of frailty and sarcopenia are separate but complementary to the optional musculoskeletal substudy discussed later in the manuscript.

#### Six-Minute Walk Test

Functional exercise capacity will be assessed using a 6MWT according to established guidelines in all participants.^33^ Participants will be advised to wear comfortable clothing and shoes prior to attending their visit. The 6MWT will be performed by a trained clinical member of research team blinded to treatment allocation. Participants will be allowed rest for 10 min prior to the 6MWT, conducted in a 6 m hallway with 3 m interval cones, facilitating back-and-forth walking at a self-determined pace and the same protocol will be employed on all recruitment centres. The distance traversed is determined by the number of completed laps multiplied by the corridor length. Dyspnoea will be assessed using Borg’s scale at the start and finish.

#### Accelerometery

A 7-day accelerometery will be performed at baseline and 12 weeks to assess change in daily physical activity and sedentary time. Participants will be required to wear an accelerometer watch on their non-dominant wrist for seven consecutive days and keep a daily log of their sleep and wake times, including periods when the accelerometer is removed. After 7 days, they will return the log and accelerometer in a prepaid envelope. Acceleration data, captured at 100 Hz, will be analysed using commercially available software.

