### Randomisation

Randomisation (1:1) will occur at the end of the baseline visit after data collection, using the ‘blockrand’ package in R^61^within the REDCap (Research Electronic Database Capture) system . The allocation list will be concealed from the user and non-editable once uploaded. REDCap’s randomisation module will reveal participant allocation only at the moment of randomisation, ensuring strict allocation concealment. The randomisation will be stratified by sex, ethnicity and baseline SGLT2-i use.

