### Study interventions

#### Baseline optimisation of medical therapy for heart failure

All eligible participants entering the study will be offered a sodium glucose co-transporter 2 inhibitor (SGLT2-i), if not already prescribed, in line with the current National Institute for Care and Clinical Excellence guidance.^27^ There will be an approximate 4-week interval between the commencement of SGLT2-i and the start of MRP to take effect in order to observe its full metabolic and CV outcome impact.^27^ Given the evidence of benefit of SGLT2-i in HFpEF and the low risk of hypoglycaemia and hypotension is minimal,^32^ SGLT2-i will not be stopped during MRP. Individuals with underlying type 2 diabetes mellitus will be provided ketone measuring strips on initiation of MRP.

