### Maintenance of weight loss

Food reintroduction/maintenance phase (week 12 to month 12)Stepped food reintroduction or transition period (eg, carbohydrate and fat reintroduction for the low carb and low fat diet options) will be individualised to participants and delivered by Counterweight dieticians.Standard evidence-based behaviour change techniques including self-monitoring (of behaviours and behavioural outcomes), goal-setting and self-rewards, action-planning, problem-solving will be employed.Digital delivery with monthly dietitian/coach support, text chat (individual and group), in-app weekly monitoring and reminders will be available to participants for up to 12 months after completing the study. The dietitian/coach support is flexible and can be tailored to individual participants, based on their needs.

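### The stated sequence puts the seven-day baseline accelerometer wear after open-label allocation for any participant with a single-day baseline visit, and the follow-up wear probably after the week-12 visit

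*Protocol article*

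**What the plan says.** All references are to the protocol article.

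- **Accelerometery:** "A 7-day accelerometery will be performed at baseline and 12 weeks to assess change in daily physical activity and sedentary time". The watch is worn for seven days in a row with a daily log, and then: "After 7 days, they will return the log and accelerometer in a prepaid envelope". The day of issue and the first day of wear are not given.
- **Assessments at baseline and week 12 visits**, the section that contains accelerometry: "The following assessments will be conducted in a single or split visit depending on the participant’s preference".
- **Study visits:** "Participants will have the option to split the baseline and 12-week visits into two visits in close succession". Table 1 in that section puts eligibility, consent and accelerometry at the baseline visit, and accelerometry again at week 12. It gives a ±3-day window for the week-12 visit. It shows health coaching in both arms at baseline and in the control arm only afterwards.
- **Baseline visit:** phenotyping follows confirmation of eligibility and written consent.
- **Randomisation:** "Randomisation (1:1) will occur at the end of the baseline visit after data collection".
- **Trial design:** AMEND-preserved "is an open-label, multicentre, randomised controlled trial".
- **Study outcomes, Table 2:** physical activity by accelerometry is both a secondary objective and a key secondary endpoint, defined as a change from baseline to 12 weeks.
- **Statistical analysis:** changes in key secondary outcomes are compared by linear regression with the stratification factors.

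**The concern.** A baseline measurement should be fixed before the participant knows the arm. If the watch goes on at the baseline visit and allocation is disclosed at the end of that visit, the baseline week becomes a post-randomisation measurement in an unblinded trial. Participants who know whether they are about to start a diet programme may move more or less that week. Control-group advice promotes physical activity, which is the behaviour being recorded.

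A between-arm difference in that week passes into the endpoint whether the analysis takes a simple change or adjusts for baseline. Randomisation no longer protects the comparison, and later analysis cannot recover a true pre-allocation baseline.

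The second wear raises a related question. If it starts at the week-12 visit, it follows a visit at which control participants are coached again, paused medicines are reassessed, and food reintroduction begins for those still on the meal-replacement plan.

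**Working it through.** There is no stated figure to reproduce; the check is one of sequence.

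**Baseline wear.** Call the day of consent day 0.

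1. Wear cannot start before day 0, because consent precedes the assessments (Baseline visit; Table 1).
2. With a single-day visit, randomisation is also on day 0 (Randomisation).
3. Wear from the next day covers days 1 to 7, so 0 of 7 days precede allocation. If the watch goes on during the visit, wear covers days 0 to 6 and only part of day 0 precedes allocation.
4. With a split visit and the watch put on at the first part (days 0 to 6), wear is complete before allocation only if the second part falls on day 7 or later. The article offers splitting as an option and says only that the two parts are close together.

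So for a single-day visit the Accelerometery and Randomisation sections cannot both hold as written. Either the baseline wear is not part of the data collected before randomisation, or randomisation is not at the end of the visit.

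**Week-12 wear.** Assume the second watch is issued at the visit and worn from the next day, with week 12 as day 84 and the visit at 84 ±3.

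| Visit day | Wear days | Wear days after day 84 | Wear days within 81–87 |
|---|---|---|---|
| 81 | 82–88 | 4 | 6 |
| 84 | 85–91 | 7 | 3 |
| 87 | 88–94 | 7 | 0 |

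Under this assumption every wear day follows the visit. The last column is descriptive only, because the ±3 days is a window for the visit and not for the wear. If the watch is worn in the week before the visit, the problem does not arise.

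**How a post-allocation baseline acts on the estimate.** Let δ12 be the true between-arm difference in week-12 activity, δ1 the difference already present in the post-allocation baseline week, and ρ the within-arm slope of week-12 on baseline activity.

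- Change score: expected estimate = δ12 − δ1
- Baseline-adjusted: expected estimate = δ12 − ρ·δ1

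Write δ1 = f·δ12. The fractions of δ12 retained are 1 − f and 1 − ρf. The documents give neither f nor ρ, so the values below are assumptions, with ρ = 0.6 throughout.

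| f (assumed) | Change score, 1 − f | Adjusted, 1 − 0.6f |
|---|---|---|
| 0.5 | 0.50 | 0.70 |
| 0 | 1.00 | 1.00 |
| −0.5 | 1.50 | 1.30 |

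A first-week shift in the same direction as the later effect shrinks the estimate. A shift in the opposite direction inflates it.

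**The case against.** The strongest reply is that the article never says when the watch is issued. Issue dates are operational detail that a journal article leaves to the full protocol, and randomising after data collection could be read as placing the baseline wear before allocation. The watch might be sent out beforehand or worn between split visits. Part of this stands: the start day is not stated, and a sufficiently spaced split visit would work. Sending the watch out beforehand, however, conflicts with consent and phenotyping starting at the baseline visit, and splitting is optional. For the single-day visit, what remains is a conflict between stated sections, not an omitted detail.

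Three stronger inferences are tempting, and the documents do not support them.

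- *Both wear weeks lie outside their intended windows.* No window is defined for the wear, and the week-12 timing is only inferred from the postal return.
- *Participants on the meal-replacement arm are already dieting during the baseline wear.* For those newly started on an SGLT2 inhibitor, "There will be an approximate 4-week interval between the commencement of SGLT2-i and the start of MRP". The Meal replacement plan section also describes referral to the provider and a medication review before the diet. No interval is stated for existing users, so the point is open either way. Baseline coaching goes to both arms, so it does not by itself create a between-arm difference.
- *The follow-up week fails to measure life on the diet.* The objective concerns weight loss brought about by the plan, and a week just after the visit still reflects the reduced weight. Participants who meet the target may stop at week 8, so wear before the visit would not capture dieting for them either.

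It is also fair that this is one of many key secondary endpoints, and that the text list under Key secondary outcomes does not repeat it.

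**Conclusion.** The point holds for the baseline wear and conditionally for the follow-up wear. For a single-day baseline visit, the stated order puts essentially the whole baseline activity week after open-label allocation, so the Accelerometery and Randomisation sections conflict. The follow-up week falls after the week-12 visit only if the second watch is issued there, which the prepaid return suggests but does not establish.

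The bias in the physical-activity comparison cannot be sized from the documents. Losses of 50% or 30% of the effect follow only from the assumed f = 0.5 and ρ = 0.6, and the sign reverses if f is negative. They show the mechanism and are not an estimate.

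The consequence is confined to the accelerometry endpoint. The six-minute walk primary endpoint is unaffected. The change is worth making, because a baseline recorded after allocation cannot be replaced at analysis.

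**What to change.** 1. Reconcile the Accelerometery and Randomisation sections by stating when each wear week starts and ends relative to allocation and to the week-12 visit.
2. Complete the baseline wear before allocation is revealed. Either issue the watch at the first part of a split visit and hold the second part after the seven days, or run the REDCap randomisation remotely once the seven days are complete.
3. Post the second watch so that wear covers the seven days before the week-12 visit.
4. For participants whose baseline wear followed allocation, compare week-12 activity between arms adjusted for sex, ethnicity and baseline SGLT2-inhibitor use. Do not use that wear in a change score or as a covariate.

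The cost is one extra postage per participant, about a week between the baseline visit and allocation, and probably a few participants consented but not randomised. The other baseline measurements would also sit about a week before allocation. Under Current status and timescale, 24 of the planned 110 had been randomised at submission, so 110 − 24 = 86 were still to come at that time. If allocation cannot be delayed, items 1, 3 and 4 can still be adopted; activity is then compared at follow-up without a baseline, with some loss of precision.
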